The administration of DSF and nutritional copper supplement is scheduled to start concomitant with alkylating chemotherapeutic treatment. Patients will take DSF (Antabus
^®^) as a once daily oral dose of 400 mg, based on the known toxicity profile
^9^. In case of intolerance, dose reduction to 200 mg per day is allowed. Copper supplementation will be administered separately from DSF with DSF administration in the evening. Copper nutritional supplement will correspond to 2.5 mg of elementary copper, which is not considered a safety concern
^23^. Adherence to treatment will be assessed at each control with a reminder, self-reporting of drug intake and drug tablet count of remaining DSF. The only surveillance of nutritional copper intake is by self-reporting.

Before study closure no crossover from the control group to DSF-Cu is allowed.

The intervention should continue also after change of chemotherapy, or during temporary chemotherapy withdrawal due to reached maximal cumulative dose or side effects from chemotherapy.

Patients are to discontinue permanently the treatment with DSF-Cu for any of the following reasons:

 Unacceptable adverse effect(s) as judged by the treating doctor. No longer indication for tumor targeted therapy. The patient wishes to withdraw from treatment. If patients develop conditions that contribute to excess risk as judged by the treating physician.

Other experimental therapy, including compassionate use programs, are not allowed in either treatment group as long as the patient is in the trial and receives the assigned treatment.

***Outcomes*.** The primary end-point of the study is survival assessed at 6 months post-randomization.

Secondary end-points are:

 Overall survival from date of randomization. Median progression free survival. 6 and 12 month progression free survival. Health-related generic quality of life
^24^. Volumetric growth rate assessed from baseline MRI to first follow-up MRI scan
^25^. Safety assessment (toxicities).

***Participant timeline*.** To reduce patient burden, timing of data collection after randomization is scheduled according to choice of chemotherapy regimen, where patients that receive temozolomide usually are assessed every 4
^th^ week while patients treated with PCV/lomustine are assessed every 6
^th^ week. Consequently, this may lead to four additional observations in the temozolomide group compared with the lomustine/PCV group. The more detailed clinical control and MRI assessment every 3

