### Data collection, management and analysis

***Data collection*.** Patients will be in the trial for a maximum of 24 months or until death (see study schedule in
Table 2). Generic quality of life is followed every 3
^rd^ month using EQ-5D 3L. Quality of life will be monitored until progression, death or 24 months post-inclusion
^24,
27^.

MRI scanning will be performed at a minimum of every 3
^rd^ month. MRI assessment may continue up to 24 months post-inclusion and this should be implemented also after documented progression in the DSF-Cu group, as long as the patient continues on only DSF-Cu, or in combination with another established rescue therapy such as surgery, radiation therapy or other alkylating chemotherapy. Consequently, MRI controls are indicated and should be continued as long as tumor targeted therapy is administered (both in control and intervention group). The RANO criteria is used in MRI assessment and for evaluation of progression
^28^.

After withdrawal of tumor target therapy no additional follow-up (including MRI) is planned within the context of this study, in order to minimize patient burden in the end of life setting. Safety assessment are according to the Common Terminology Criteria for Adverse Events (CTCAE) version 4.0
^29^. Survival is followed until death or 24 months post-inclusion.

***Data management*.** Data will be recorded in the web-based eCRFs (WebCRF 3.0) at The Unit for Applied Clinical Research at the NTNU. All data will be entered in the WebCRF 3.0 at the local study site. All electronic patient information is handled using a study participation number that is not logically connected to any personal data. It is possible to manually “decode” back to personal data using a name list stored securely at the respective study sites.

All data entered into the WebCRF are stored at two separate servers at NTNU. These servers are protected by the general firewall at the university and then by another firewall dedicated to protect clinical research data. The server that stores the data is not the same server as the one in contact with the Internet. There are several further safety measures not to be exposed. There are backups taken every 24-hour throughout the years. The responsibility for this system lies with the Unit for Applied Clinical Research at NTNU.

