***Statistical methods*.** All outcomes will be analyzed according to the intention to treat principle unless otherwise specified in post-hoc analyses. This is an open label trial, however the statistician performing analyses will be blinded for treatment assignment. Also, an investigator blinded for treatment allocation will perform the assessment of radiological end-points.

The 6-month survival (i.e primary end-point) will be assessed with 2x2 tables and analyzed with chi-square test. This analysis will be performed 6-months after last patient inclusion. Concerning the primary end-point we do not expect any missing data.

Concerning the secondary outcomes they will be evaluated as follows:

 Actual survival data at 24 months post-inclusion will be analyzed similar to the primary end-point. Overall survival analyses will be analyzed using Kaplan-Meier plot and tested with log-rank test. This analysis will be performed at 6 months after the last patient inclusion together with the assessment of primary outcome. Also, this will be analyzed in a longer-term follow-up study (24 months post-inclusion). Overall progression free survival will be analyzed with Kaplan-Meier plot and tested with log-rank test. This analysis will also be performed at 6 months and at 24 months after the last patient inclusion. The assessment of progression will be done in accordance with the latest RANO criteria by the local investigator. Actual progression free survival analyses at 6 and 24 months after the last patient inclusion. The assessment of progression will be done in accordance with the latest RANO criteria by the local investigator and analyzed similar to the primary end-point. Comparison of general health related quality of life at 6 and 24 months after last included patients. We will use an area under the curve approach (i.e. cumulative quality of life)
^27^. Semiautomatic segmentation of contrast-enhancing tumor volume assessed at baseline and first MRI control to assess growth dynamics. The data will be analyzed with independent samples t-test or Mann-Whitney U test, based on data distribution. Safety assessment with comparing proportion of a composite of grade 3, 4 and 5 toxicities according to the common terminology Criteria for Adverse Events (CTCAE).

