We stratify only for study center, however important baseline variables like repeated surgery, time since primary treatment, age, functional status, lomustine versus temozolomide treatment, and biomarker status from initial surgery if available (IDH and MGMT) will be registered and adjusted for in post-hoc exploratory analyses. Also, we will explore outcomes in post-hoc as treated analyses if non-compliance to treatment protocol becomes apparent.

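### The tumour-growth comparison leaves the choice of test to the observed data, does not adjust for the measured baseline volume, and has no value for patients without a first follow-up MRI

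*Protocol article*

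**What the plan says.** - The Outcomes paragraph lists as a secondary end-point "Volumetric growth rate assessed from baseline MRI to first follow-up MRI scan".
- Statistical methods describes the measurement as "Semiautomatic segmentation of contrast-enhancing tumor volume assessed at baseline and first MRI control to assess growth dynamics" and then gives the comparison: "The data will be analyzed with independent samples t-test or Mann-Whitney U test, based on data distribution". It states no rule for choosing between the tests and names no covariate.
- The same section opens with "All outcomes will be analyzed according to the intention to treat principle unless otherwise specified in post-hoc analyses". Its expectation of no missing data is confined to the primary end-point.
- It also says that "the statistician performing analyses will be blinded for treatment assignment" and that "an investigator blinded for treatment allocation will perform the assessment of radiological end-points".
- The closing paragraph of Statistical methods lists baseline variables that "will be registered and adjusted for in post-hoc exploratory analyses". Tumour volume is not among them.
- Table 2 places the first scheduled follow-up MRI at month 3. Data collection adds: "After withdrawal of tumor target therapy no additional follow-up (including MRI) is planned within the context of this study". It also allows scanning to go on after progression in the DSF-Cu group while the patient takes DSF-Cu alone.

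**The concern.** Three features of this one comparison deserve attention.

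1. **Test chosen on the data.** A t-test compares mean growth. A Mann-Whitney test compares ranks. Until the distribution is inspected, nobody can say which of the two the trial will report.
2. **Baseline volume unused as a covariate.** The trial segments volume at baseline, and that value may help to predict later growth. Leaving it out of the model gives up precision in a trial of 142 patients.
3. **Value defined only for scanned patients.** A growth rate needs two scans. A patient who dies, or whose scanning ends, before the first control has no value, and neither named test can include that patient. If such patients tend to have fast-growing tumours and are more numerous in one arm, the two groups compared are no longer the randomised groups.

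The trial is meant to supply preliminary evidence and a basis for later power calculations. A blurred or shifted growth estimate would therefore be carried into later planning.

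**Working it through.** **Plan's own figure.** No effect size, SD or scan-loss rate is stated for growth. The survival inputs used below come from Sample size and study power, whose figure reproduces. With 60% versus 80%, two-sided alpha 0.10 and power 80%:

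n = [1.645 × √(2 × 0.7 × 0.3) + 0.842 × √(0.6 × 0.4 + 0.8 × 0.2)]² / 0.2² = (1.066 + 0.532)² / 0.04 ≈ 63.9, so 64 per arm and 128 in total. Then 128 / 0.9 = 142.2, against 142 stated.

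**Test choice.** Null data were simulated with 60 patients per arm and 8,000 repetitions. The t-test was used if a Shapiro-Wilk test on the pooled residuals gave p > 0.05, and the Mann-Whitney test otherwise. Type I error at nominal 0.10 was:

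| Distribution | Type I error |
|---|---|
| Normal | 0.100 |
| Lognormal | 0.093 |
| t with 3 df | 0.103 |

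The error rate is essentially kept. The cost is the open estimand.

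**Baseline adjustment.** Let log volumes at the two scans have equal variance σ² and correlation ρ. The change score has variance 2σ²(1 − ρ). After adjustment for baseline the variance is σ²(1 − ρ²). The ratio is (1 + ρ)/2.
- ρ = 0.6: ratio 0.80, a 20% reduction.
- ρ = 0.8: ratio 0.90, a 10% reduction.

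The documents give no ρ, so this range is an assumption.

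**Loss before the first scan.** Assume exponential survival, so S(3) = √S(6).
- Control: 1 − √0.60 = 0.225, or 16.0 of 71.
- DSF-Cu: 1 − √0.80 = 0.106, or 7.5 of 71.
- Cross-check for control from the 8-month median on lomustine cited in the same section: 1 − 0.5^(3/8) = 0.229.

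**Shift in the comparison.** Let growth be standard normal, let loss depend on a normal score correlated r with growth, and let a fraction f be lost. With c = Φ⁻¹(1 − f), the mean among scanned patients is displaced by −r·φ(c)/(1 − f).
- Control, f = 0.225: −0.388r.
- DSF-Cu, f = 0.106: −0.204r.
- Difference: about 0.18r SD. With f = 0.229 for control it is 0.393 − 0.204 = 0.19r SD.

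| Growth-loss correlation r | Shift against DSF-Cu, f = 0.225 vs 0.106 (SD) |
|---|---|
| 0.3 | 0.055 |
| 0.5 | 0.09 |
| 0.8 | 0.15 |
| 1.0 | 0.18 (0.19 with f = 0.229) |

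A simulation of the same model gave 0.052, 0.091, 0.145 and 0.179. With equal loss and the same selection in both arms, the shift is 0.

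For scale, about 55 control and 63 or 64 DSF-Cu patients would be scanned. The standard error of the difference is then √(1/55 + 1/63.5) ≈ 0.18 SD, so 0.09 SD is about half a standard error.

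**The case against.** The defence has several sound points.

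- **Error rate.** A reader might infer that picking the test after looking at the data makes the p-value meaningless. The simulation does not support this, and both the statistician and the radiological assessor are blinded to allocation. The objection stands.
- **Baseline.** A reader might infer that the missing adjustment biases the result. It does not. The outcome is already a change from baseline, and an unadjusted comparison is valid under randomisation. Only precision is lost, by an amount that rests on an assumed correlation.
- **Unequal loss.** A reader might infer that the fastest-growing tumours will certainly drop out more often in one arm. The document does not say so. It takes a survival difference, or a difference in when scanning stops, together with a link between growth and loss. The provision for scanning on DSF-Cu alone could produce some imbalance without a survival effect, but nothing in the article quantifies it.
- **Size.** The 0.19 SD figure needs perfect correlation. Constant hazard from day 0 may overstate early deaths in patients selected on performance status and blood counts. Three months is the longest scan interval allowed, so some first scans may come earlier. The shift also runs against DSF-Cu if DSF-Cu prolongs survival, so on that route it would hide a benefit and not create one.
- **Unseen documents.** Handling of missing scans and a rule for the test may be in the full protocol or the SAP. That is fair as far as silence goes. But the article does state a data-dependent choice of test, and it does state intention to treat for all outcomes next to an end-point that cannot be computed for all patients. Those two statements can be judged as they are.

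**Conclusion.** The point holds as an inexpensive improvement to a secondary analysis. As written, the growth comparison leaves open whether means or ranks are compared, and it forgoes a gain of about 10-20% in variance if log volumes correlate at 0.6-0.8. It also covers only scanned patients, although all outcomes are declared intention to treat.

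Under the design survival rates, exponential survival, normally distributed growth and growth-loss correlations of 0.3-0.5, the selection may shift the result against DSF-Cu by about 0.05-0.09 SD. The ceiling is about 0.19 SD, and the shift is zero if loss is balanced. The documents do not support calling the p-value invalid, calling the unadjusted test biased, or treating unequal dropout as established. The primary end-point, the sample size and the survival analyses are not touched.

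**What to change.** 1. Delete the clause that makes the test depend on the distribution, and name one analysis: a linear model of log-volume growth rate (change in log volume per unit time) on arm, with log baseline volume and centre as covariates.
2. State a rule for near-zero volumes, since the log scale is sensitive there and repeated surgery is among the registered variables. Do not add days between scans as a covariate: it arises after randomisation, treatment may affect it, and the rate already accounts for time.
3. This model still uses only scanned patients. Say so, and add one sensitivity rank analysis in which patients who died before the first follow-up MRI, or had tumour-targeted therapy withdrawn before it, take the worst rank.
4. Report the number of missing first follow-up scans by arm.

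**Cost.** Wording and one extra analysis. Volumes, survival and treatment discontinuation are already recorded, and no new scans or patients are needed. The worst-rank result partly reflects survival, and so overlaps with the survival end-points. It should be labelled so and not read as a pure effect on growth.

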Based on the assumption that the treatment group will have an improvement in proportion achieving 6-month survival from 60% to 80% we need a final sample size of 128 in total (64 in each group; alpha 0.1, power 80% and two sided test). Considering 10% attrition, the actual included sample need to be 142 with 71 patients included in each group.

***Assignment of interventions*.** A web-based randomization system (WebCRF 3.0) developed and administered by the Unit of Applied Clinical Research, Faculty of Medicine and Health Sciences, Norwegian University of Science and Technology (NTNU, Trondheim, Norway), will be used. Randomizations are computer generated in a 1:1 ratio with stratification by center. Blocks of varying sizes will be used to make prediction of allocation impossible. Randomization will be performed only after the initial chemotherapy treatment has been selected. Patient enrollment is performed by a study member with appropriate delegation at the local site.

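### The primary chi-square is valid and adequately powered, but adjustment for baseline factors the protocol calls important is left to post-hoc analyses, so available precision goes unused

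*Protocol article*

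**What the plan says.** All references are to the protocol article.

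- **Primary analysis** (Statistical methods): "The 6-month survival (i.e primary end-point) will be assessed with 2x2 tables and analyzed with chi-square test". No covariate or stratum is mentioned.
- **Randomisation** (Assignment of interventions): "Randomizations are computer generated in a 1:1 ratio with stratification by center". Study setting lists eight centres. Chemotherapy is chosen before the patient is randomised.
- **Baseline factors** (last paragraph of Statistical methods): centre is the only stratification factor. Repeat surgery, time since primary treatment, age, functional status, lomustine or temozolomide, and IDH and MGMT where available are described as important. They "will be registered and adjusted for in post-hoc exploratory analyses". They are given as examples, so the set is not closed.
- **MGMT**: the Introduction describes it as an important predictive biomarker.
- **Sample size** (Sample size and study power): 60% against 80% alive at 6 months, with "alpha 0.1, power 80% and two sided test", leading to "we need a final sample size of 128 in total" and 142 enrolled after 10% attrition.

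The article names no adjusted or stratified analysis as primary, supporting or sensitivity analysis.

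**The concern.** Covariates named before the data exist are assigned to analyses called post-hoc. The label takes evidential weight from an analysis that is in fact foreseen. It also leaves the choice of covariates open in an open-label trial.

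Two things are at stake. Adjusting for prognostic baseline variables usually raises power at the same sample size, and the plan does not use this. And with only centre balanced by design, arms of 64 to 71 patients can differ visibly in a prognostic factor. If they do, the only foreseen response is an analysis that readers have been told to treat as exploratory. The Discussion says the result will also feed power estimates for later studies, so a more precise estimate has value beyond the test itself.

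**Working it through.** **1. The plan's own figure.** Pooled-variance formula without continuity correction, with p1 = 0.60, p2 = 0.80, mean 0.70, z(0.95) = 1.645, z(0.80) = 0.842:

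n per arm = [1.645 × √(2 × 0.70 × 0.30) + 0.842 × √(0.60 × 0.40 + 0.80 × 0.20)]² / 0.20² = (1.066 + 0.532)² / 0.04 ≈ 63.9, so 64 per arm and 128 in total.

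Attrition: 128 / 0.9 = 142.2, against 142 stated. Power is 80.1% at 64 per arm and 83.6% at 71. The planned test delivers the planned power.

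**2. What adjustment adds.** The documents do not give the prognostic strength of the factors or the variation between centres; both are assumptions here, shown as ranges. Simulation: N = 128, 4,000 trials per scenario, eight equally likely centres, permuted blocks of 2 or 4 within centre, marginal survival held at 60% and 80%, and at 70% in both arms for the null. The adjusted test is a logistic likelihood-ratio test with one prognostic score. CMH is the Cochran-Mantel-Haenszel test by centre.

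| SD of score (log-odds) | SD of centre (log-odds) | Power: chi-square | Power: CMH | Power: adjusted | Null: chi-square | Null: CMH | Null: adjusted |
|---|---|---|---|---|---|---|---|
| 0 | 0 | 0.811 | 0.806 | 0.808 | 0.102 | 0.097 | 0.103 |
| 0.5 | 0 | 0.799 | 0.796 | 0.817 | 0.098 | 0.094 | 0.100 |
| 1.0 | 0 | 0.819 | 0.813 | 0.868 | 0.100 | 0.097 | 0.101 |
| 1.5 | 0 | 0.809 | 0.809 | 0.905 | 0.106 | 0.106 | 0.112 |
| 0 | 0.5 | 0.809 | 0.820 | 0.809 | 0.104 | 0.109 | 0.107 |
| 1.0 | 0.5 | 0.811 | 0.816 | 0.862 | 0.101 | 0.104 | 0.099 |
| 1.5 | 0.5 | 0.822 | 0.829 | 0.908 | 0.105 | 0.104 | 0.106 |

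The Monte Carlo standard error is √(0.8 × 0.2 / 4000) = 0.006 for power and √(0.1 × 0.9 / 4000) = 0.005 for the null. With no centre variation, the gain from adjustment is about 0, 2, 5 and 10 points for SD 0, 0.5, 1.0 and 1.5. Stratifying by centre alone changes power by about −0.5 to +1 point.

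**3. A realistic covariate set.** A single known score flatters adjustment. Further simulations used age, Karnofsky status, chemotherapy type and three-level MGMT, with assumed distributions.

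- The gain was about 0 to 8 points for SD 0 to 1.5, with type I error about 1 point above that of the chi-square when centre was left out.
- With eight centres as fixed terms, type I error rose by about 1 to 3 points above the chi-square, to about 0.11–0.14. In one run at N = 142 with SD 0.5 / 0.8 / 1.0 and 60% survival in both arms, it was 0.129 / 0.134 / 0.110, against 0.115 / 0.117 / 0.099 for the chi-square. Part of that model's apparent power is therefore inflated alpha.

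**4. Information available.** Expected deaths by 6 months under the design rates are 64 × 0.40 + 64 × 0.20 = 38.4, or 71 × 0.40 + 71 × 0.20 = 42.6. About 38 to 43 events support only a few covariates.

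**5. Chance imbalance at 64 per arm.** For a factor with 40% prevalence, SE = √(2 × 0.40 × 0.60 / 64) = 0.087. The arms then differ by more than 10 points in 24.8% of trials and by more than 15 points in 8.3%. At 50% prevalence the figures are 25.8% and 9.0%. As an illustration, if such a factor separates 6-month survival by 30 points (assumed), a 15-point imbalance moves the observed difference by 0.15 × 30 = 4.5 points, against a target of 20.

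**The case against.** The strongest reply is that nothing here is wrong. The chi-square is valid under randomisation and matches the sample size calculation, and the trial meets its stated power. Adjusted analyses and their covariates are already mentioned. The gain depends on prognostic strength that the documents do not state, and could be nil. MGMT and IDH may be missing for many patients. Changing the primary test when 36 patients had already been randomised is a protocol modification, not an edit of wording. All of this stands, and it limits the point to unused efficiency.

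A reader might infer three stronger claims, none of which the documents support:

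- **That the trial is underpowered.** It is not: the stated size reproduces, and the comparison is with what adjustment could add.
- **That imbalance would confound the unadjusted result.** Chance imbalance after randomisation is random error, already covered by alpha. Adjustment reduces that error; it does not remove a bias.
- **That leaving out centre distorts the test.** Simulated type I error of the chi-square was 9.8–10.6% in step 2, and centre is worth about 1 point of power or less.

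The reply fails on one matter. These choices have not been left to the statistical analysis plan: the article settles both the primary test and the exploratory status of adjustment. A later plan could raise that status only by departing from it.

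**Conclusion.** The point holds as a worthwhile, inexpensive improvement, not as an error in the plan. The primary analysis is valid and adequately powered, but it leaves unused covariates that the protocol itself calls important and already records. The size is about 0 to 8–10 points of power at the planned sample size. It rests on an assumed combined log-odds SD of 0 to 1.5, on assumed covariate distributions and on equal centre sizes. If the factors are weakly prognostic, the gain is 0 to 2 points. The post-hoc label is inapt whatever the gain, because the factors are named in advance.

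**What to change.** Before any unblinded data are seen, including the interim analysis at 71 patients:

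1. Prespecify a covariate-adjusted analysis of 6-month survival with a short closed list, for example age, Karnofsky status, chemotherapy type, and MGMT with an unknown category so that no patient is dropped.
2. Report it as a standardised risk difference with confidence interval, tested at two-sided alpha 0.10. Make it the primary analysis or, at minimum, the named key supporting analysis.
3. Keep the chi-square alongside it, and remove the post-hoc label for this set.
4. Handle centre by stratification, pooling or a random intercept, not by eight fixed terms. The random intercept was not among the models simulated here, so check its type I error before adopting it.

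**Cost.** No extra data. The headline becomes model-based instead of a plain 2x2 table. Type I error may rise by about 1 point in small samples unless a small-sample or permutation reference is used. The change must be reported to the ethics committees and, if judged significant, to both medicines agencies, as Ethical considerations requires.
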